### Sample size

The sample size is based on finding an effect on the primary outcome of the intervention, perceived fatigue. Fatigue will be measured using the 20-item CIS questionnaire [43]. The mean total score on this questionnaire for healthy employees is 47.3 (SD = 19.8) according to Beurskens et al. [43] (score range 0–140). Power calculations indicate that to detect a relevant 10% difference in fatigue, 246 subjects are necessary in each study group (with power = 0.80 and alpha = 0.05). Taking the expected loss to follow-up (25%) into account, a sample size of approximately 656 employees is required.

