#### Primary outcome

The primary outcome variable is fatigue. Fatigue will be measured using the 20-item Checklist Individual Strength (CIS) [31]. The questionnaire consists of four dimensions; the subjective experience of fatigue, reduction in motivation, reduction in activity, and reduction in concentration. It has been found that the questionnaire has a good internal consistency: the Cronbach’s α for the total CIS was 0.90 and for the scales the α ranged from 0.83 to 0.92 [31].

The questions have seven answer options, ranging from “yes that is correct” to “no that is not correct”.

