### Statistical analysis

To investigate the success of the randomisation procedure, potential confounders or effect modifiers (age, gender, type of aircraft flown, household composition, morningness-eveningness) will be compared between the intervention and control group by Student t-tests for independent samples and Chi square tests (χ2).

The effectiveness of the intervention (time*group interaction) will be analysed using linear mixed model analyses with the outcome measures at follow-up (T1-T2) as the dependent variables. The dependent variables are fatigue, sleep, physical activity, nutrition, need for recovery, sickness absence, work-private life balance, general health and knowledge, whereas research condition (intervention or control group) is the independent variable. Possible confounding or mediating factors will be considered.

A detailed analysis plan will be developed prior to finalisation of the dataset. For all analyses a two-tailed significance level of <0.05 will be considered statistically significant. The analyses will be performed using PASW 20.0 (SPSS Inc. Chicago, Illinois, USA).

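### The planned 246 per group gives about 75% power, not 80%, for a 10% difference in CIS fatigue; it fits a 5-point (10.6%) difference

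*Protocol article*

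**What the plan says.** The Sample size section of the protocol article ties the calculation to the primary outcome: "The sample size is based on finding an effect on the primary outcome of the intervention, perceived fatigue". It takes its reference values from a study of healthy employees: "The mean total score on this questionnaire for healthy employees is 47.3 (SD = 19.8". The target is relative, and no figure in points is given: "to detect a relevant 10% difference in fatigue, 246 subjects are necessary in each study group (with power = 0.80 and alpha = 0.05". After an allowance for 25% loss to follow-up, it concludes that "a sample size of approximately 656 employees is required".

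The Statistical analysis section settles the sidedness: "For all analyses a two-tailed significance level of <0.05 will be considered statistically significant". It plans a linear mixed model on the three- and six-month outcomes. The Sample size section mentions no correlation between measurements, no baseline adjustment and no gain from repeated measures.

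The Sample size section also prints a score range of 0 to 140. The Primary outcome section describes 20 items and says of them: "The questions have seven answer options".

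**The concern.** Every input to a two-group comparison of means is on the page, so 246 should reproduce. It does not: the number is too small for the difference that the protocol calls relevant.

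This is the only power statement for the primary outcome. If the trial finds no effect, a reader relying on it would take the chance of missing a true 10% reduction to be 20%. On the stated inputs it is about 25%.

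The printed score range adds a smaller problem. Twenty items with seven consecutive integer scores run from 20 to 140 (scored 1 to 7) or from 0 to 120 (scored 0 to 6), never from 0 to 140. A percentage of a mean depends on where the scale starts, so a relative target is less clear when the origin is in doubt.

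**Working it through.** **Inputs.** All come from the protocol article.
- Mean 47.3, SD 19.8, 10% difference, power 0.80, alpha 0.05, 246 per group, 25% loss: Sample size.
- Two-sided testing: Statistical analysis.
- Difference in points: 0.10 × 47.3 = 4.73. Standardised: 4.73 / 19.8 = 0.239.

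**Formula.** For two equal groups, n per group = 2 × (z for alpha/2 + z for power)² × SD² / difference², with z values 1.960 and 0.842.

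**The plan's own figures**
- Loss to follow-up: 246 / 0.75 = 328 per group, and 2 × 328 = 656. This reproduces.
- 246 per group from a 5.0-point difference: 2 × (1.960 + 0.842)² × 19.8² / 5.0² = 246.2. This reproduces, but 5.0 / 47.3 = 10.6%, not 10%.

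**The stated 10% difference**
- 2 × (1.960 + 0.842)² × 19.8² / 4.73² = 275.1, so 276 per group after rounding up. The t-based calculation gives 276.0.
- Shortfall: 276 − 246 = 30 per group, or 12% of 246.
- Total after 25% loss: 276 / 0.75 = 368 per group, 736 in all. That is 736 − 656 = 80 more than stated.

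**Power at 246 per group.** Power = Φ(difference × √(n/2) / SD − 1.960).

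| Difference | Argument of Φ | Normal | t-based |
|---|---|---|---|
| 4.73 points (10%) | 4.73 × √123 / 19.8 − 1.960 = 0.69 | 75.5% | 75.3% |
| 5.0 points (10.6%) | 5.0 × √123 / 19.8 − 1.960 = 0.84 | 80.0% | 79.8% |

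The difference detectable with 80% power is (1.960 + 0.842) × 19.8 × √(2/246) = 5.00 points.

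**Other readings of the stated inputs**
- One-sided 5% test at 4.73 points: 217 per group.
- 10% of the scale range: 32 per group for 14 points, 43 for 12 points.
- SD falling in proportion to the mean in the intervention group: 249 per group.
- Ratio-scale formula with coefficient of variation 19.8 / 47.3 = 0.419 and log(0.9): about 248 per group.

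The last two come close, but nothing in the document points to them, and 5.0 points fits better. That 4.73 was rounded up to 5 is an inference about how the number arose. The mismatch itself does not depend on it.

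**The case against.** The strongest reply is that 75% describes an unadjusted comparison at one time point, while the trial plans a mixed model on two follow-ups.
- If the analysis adjusted for the baseline score, the required n would fall by the factor 1 − r², where r is the correlation between baseline and follow-up. Then 246 suffices for 4.73 points once r is at least about √(1 − 246/276) = 0.33.
- If the tested effect were the average over three and six months, the factor would be (1 + r)/2, with r now the correlation between the two follow-ups. Then 246 suffices if r is below about 0.79.

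Both are plausible, and actual power may well reach 80%. So the 75% should be attached to the simple comparison that the stated inputs imply. But the Sample size section claims neither gain and states no correlation, and the Statistical analysis section does not name the baseline score as a covariate. It also refers to a time-by-group interaction; if that is the contrast tested, power could move in either direction. A possible gain that the calculation does not use cannot make its stated result correct.

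The second reply is that the gap is small: 5.0 against 4.73 is 0.27 points on a 20-item scale, and the loss figure is itself a guess. If loss were about 16% (276 / 328 = 0.84 retained), the planned 656 would give 80% power for 4.73 points; with no loss, power would be about 86%. This is fair as to size. The protocol, however, plans for 25% loss and names 246 as the number needed.

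Third, the score range enters no step of the calculation. That is right: 10% of the stated mean is 4.73 whatever range is printed. The range is a side correction.

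**Conclusion.** The concern holds. On the protocol's own mean, SD, significance level and relative target, 246 evaluable pilots per group give about 75% power for a 10% difference. They give 80% only for about 5.0 points, or 10.6%. A true 10% target at 80% power needs 276 evaluable per group and 736 randomised.

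This assumes an unadjusted two-group comparison of means with a common SD of 19.8, equal groups and a two-sided 5% level. The shortfall is moderate, about 5 percentage points of power, and the planned model may recover it. It does not call the design into question, but the power statement as written is incorrect and should not stand.

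**What to change.** Restate the target in points, for example: 246 evaluable pilots per group give 80% power to detect a 5.0-point difference in CIS total score (10.6% of 47.3, SD 19.8), and about 75% power for 4.73 points (10%), in an unadjusted two-group comparison at a two-sided 5% level. The 656 then stands. Correct the score range to match the item scoring actually used, and check that 47.3 is on that scoring. The cost is wording only, with a slightly less favourable power claim.

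If the sponsor prefers to keep 10% at 80% power with 246 per group, the paragraph should base the calculation on a baseline-adjusted analysis and show the assumed correlation (at least about 0.33). The Statistical analysis section would then have to name the baseline score as a covariate, which goes beyond wording. Keeping 10% at 80% without adjustment would mean 736 participants, 80 more than planned.

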## Discussion

This paper describes the development of an intervention consisting of a set of tailored advices (about daylight exposure, sleep, physical activity, and nutrition) delivered through a smartphone application for airline pilots, and the design of a randomised controlled trial evaluating its effect on fatigue, health and sickness absence.

Many authors have called for additional efforts to prevent the detrimental health effects of irregular working hours among the employees involved [9,44]. Fortunately, knowledge about the influencing factors of fatigue and disturbance of the circadian rhythm is available. Since educational programs in the past generally did not show a long term fatigue reduction among flight crew, the present study tailors the advices and makes them easy obtainable. By using new forms of media, it aims to improve health behaviour, to reduce experienced fatigue, and to improve general health.

### Strengths & limitations

The fact that this intervention uses a smartphone application to transfer knowledge and aims to change behaviour is a strength. A recent estimation in the Netherlands showed that 52% of all phone users own a smartphone and this number is expected to grow to 65% in 2012 [45]. Moreover, in the specific target population of this study the percentage of smartphone users is expected to be even higher. Smartphones and tablet computers have several advantages; they are easy to use and to carry on, and do not necessarily need to have access to internet in order to work as an information source. Further, the technology of the smartphone application itself makes it possible that the advices are presented specific per function, morningness-eveningness type, and flight schedule. Evaluating smartphone apps to improve health behaviour by using a RCT is relatively new. To our knowledge, the study of Quinn et al. [46] was the first to present results of a RCT on mobile health (mHealth). In their study, positive effects were found on the control of blood glucose in diabetes patients. The number of mHealth studies is expected to rise in the upcoming years since several research protocols have been published [47,48]. Also a guideline for both eHealth (web-based interventions to improve health behaviour) and mHealth RCTs was published recently [49].

The MORE Energy study is the first randomised controlled trial that uses mHealth to improve health behaviour in flight personnel. Advantages of mHealth are partly similar to those of eHealth, and include the unique characteristics of technology (e.g. video transmission, interactiveness), its relative cost-efficiency, the immediate and easy access of information or advice, and the flexibility of user control of the intervention [50]. However, the evaluations of these kind of interventions are often complicated by the fact that a substantial proportion of participants may have dropped out because of non-use or loss to follow-up [26,49]. Because the effectiveness is dependent on participants actually using the intervention, in the current study, the usage of the application and website will be measured for each participant. Furthermore, the process evaluation will give insight in compliance, how the intervention was evaluated by participants, and how the advice was used. By tailoring the intervention to the needs of the target population through focus group discussions, it is expected that the risk for low compliance in this intervention is somewhat reduced.

The use of focus groups with the target population is also a strength. Together with the interviews with the key management stakeholders of the company, it resulted in an implementation strategy that took into account a lot of barriers faced by the target population. With this strategy, it is thought that problems faced by similar studies [19] are partly overcome. These studies used other kinds of media to transfer knowledge, and were therefore limited in their capability to tailor their advice. In the MORE Energy study, advice will not only be tailored, but will be offered in such a way that participants can choose the advices that fulfil their specific needs at specific moments.

There are possible limitations to this study as well. Firstly, results from earlier studies and indications from the focus groups point out that there might be a substantial group of pilots that will not participate because they have their own long-lasting routine to cope with flight schedules, and are not open for new insights. This will lead to selection bias [51]. Further, because the intervention will use a smartphone application, employees who do not own such a device are excluded from this study. Therefore, even though smartphones and tablets are widely used throughout pilots, a certain subgroup of employees will not be able to participate. Unfortunately, since we do not have information about who does or does not own a smartphone, we can only compare the demographic characteristics of the whole population of airline pilots with those of the participants.

Another limitation of the study is the possible crossover of information. It was decided to randomize the participants at an individual level. This means that, during a flight routine a control group pilot and an intervention group pilot with smartphone application may share the cockpit which makes contamination plausible. Because the application is personalised and both the application and website have a unique login per participant, it is assumed that contamination will have a limited effect on the resulting differences in outcome between groups though. Finally, a possible limitation is that the participants will not be blinded for design. Because the control group will receive a minimal intervention only, and the intervention group will receive extensive, specific and tailored advice (which is easily accessible through both smartphone application and website) the contrast between groups is considered sufficient however. Although we chose to offer the control group a minimal intervention rather than no intervention, more attention was given to the intervention group. Because of this, the Hawthorne effect cannot be fully excluded.

This RCT will investigate whether a tailored mobile health intervention can reduce fatigue and improve general health of airline pilots by improving the knowledge and behaviour with respect to exposure to daylight, sleep, nutrition and physical activity. If results are positive, it would provide a new tool in fatigue management, possibly reducing the health risks of irregular working times of both flight crew and shift workers. Results of the MORE Energy study will become available at the end of 2013.
